### 10.9.3. Cross-sectional analyses

Hemoglobin mean and standard deviation will be presented (following cross-sectional visit at Clinic Visit 6 and Month 14 **and Clinic Visit 9**) and 95% confidence intervals will be calculated. The effect of the group will be evaluated using a non-parametric Wilcoxon test.

For the assessment of the parasite density at following cross-sectional visit at Clinic Visits 6 and 7 **and 9**, a 2x2 table presenting the frequency of positive and negative will be

presented. The effect of the group will be evaluated using the Fisher exact test. The Geometric mean of those positive in each group will be calculated. Difference in geometric mean and 95% CI will be estimated. The effect of the group will be evaluated using a non-parametric Wilcoxon test.

*Amended 17 April 2008*

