##### **5.2.2. Screening of volunteers**

Only children with a written Informed Consent Form, signed/thumb printed and dated by parents/guardians will be screened.

Comprehension of the information contained within the Informed Consent Form will be checked prior to screening by an oral interview with the volunteer's parent(s)/guardian(s), according to SOPs at the study sites. If consent is not available from both parents/guardians, the reason for the unavailability of one of the parents/guardians will be specified on the consent form.

Subject numbers will be allocated to all volunteers who are consented for screening by their parent(s)/guardian(s). Separate lists of non-overlapping subject numbers will be provided to each site and subject numbers issued to subjects consecutively at each site.

Once consent is obtained, then per-protocol eligibility criteria will be checked, which will necessitate a physical examination and blood sampling for assessment of hematology, renal and liver function. This will be documented on clinic forms, which are prepared and filled in by the investigator. Each form will contain the subject number, information about the volunteer's date of birth, household, date of screening visit, medical history and physical and laboratory screening examination. After reviewing the medical history, physical examination and laboratory results, any reasons for non-eligibility will be documented in the CRF.

The parent(s)/guardian(s) of children who have been consented for the study and found to be ineligible will receive a full explanation by a study clinician. Any clinically relevant finding will be treated appropriately by a physician. Where necessary the child will be referred to a specialist at Coast General Hospital, Mombasa, Kenya, or KCMC Hospital in Moshi, Tanzania for evaluation and treatment as described in Section 5.7. An overview of the laboratory assays can be found in Appendix D and further details can be found in site SOPs.

A study identification card will be prepared for the parent(s)/guardian(s) of each screened subject. At screening a photograph of each screened subject being held by their parent(s)/guardian(s) will be taken and attached to the study identification card. This card will also bear the name of the study to which the child is enrolled, and the child's subject number. Parents/guardians will be instructed to come to the hospital if their child is sick and to identify their child as study participants.

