**Amended 17 April 2008**

**CONFIDENTIAL**

106464 (Malaria-049)  
Amendment 4 Final, 17 April 2008

ACD: Active Case Detection PCD: Passive Case Detection ICS: Intracellular Cytokine Staining FW: Field Worker

A The survey will be postponed in the event of low case rates occurring during the first four months of surveillance

B These visits will occur in the double blind phase in the event that the survey at Clinic Visit 6 is postponed

C all antimalarial, systemic antibiotic and antipyretic medication to be recorded

D record administration of immunosuppressants or other immune-modifying drugs during this period (for corticosteroids this means prednisone or equivalent,  $\geq 0.5$  mg/kg/day. Inhaled or topical steroids are allowed and should not be recorded. ALSO all immunoglobulins and blood products should be recorded during this period. ALSO any antimalarials.

E SAEs related to study procedures will be collected

F Procedure for PCD will be followed

Amended 20 November 2006

H If documented fever

J Where the subject is febrile, blood test, rapid test, and parasite genotyping will be performed

K Includes analysis of hemoglobin, total white cell count and platelets.

L Done only in study participants enrolled by KEMRI, Kenya

M Final analysis will be delayed in the event of low case rates occurring during the first four months of surveillance

N Visit 39 to occur between 14 days post Dose 3 of vaccine and 20 days post Dose 3 of vaccine

O Carried out on Field Worker Visit Code # 55 ONLY

P Carried out on Field Worker Visit Code # 86 ONLY

Amended 23 October 2006

Q Samples from Tanzania will be analyzed at LSHTM and/or their collaborating laboratory, at GSK Biologicals and/or their collaborating laboratory, and in Tanzania. Samples from Kenya will be analyzed at LSHTM and/or collaborating laboratory, at GSK Biologicals and/or collaborating laboratory, and in Kenya

Amended 20 November 2006

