**Clinic Visit 1: Screening**  
Day -60 to Day 0

---

- Obtain signed, dated, thumb printed informed consent from the parent(s)/guardians.
- Check inclusion/exclusion criteria.
- Carry out physical examination, take medical history, measure body weight, record vital signs.
- Assign subject number.
- Record any SAEs that may have occurred as a result of study procedures.
- Record baseline covariates.
- Blood sample to collect 5 mL blood for analysis of:
  - hematology (complete blood count).
  - biochemistry (creatinine and ALT).
  - serology (antibodies to CS, HBs, anti-blood-stage humoral immunity).
  - CMI:
    - CS-specific T-cells (ICS);
    - At KEMRI, Kenya only:* CS-specific T-cells (ELISPOT).

---

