**10.2. Secondary endpoints****Efficacy**

- Time to first case of malaria meeting the secondary case definition over a period starting 14 days after Dose 3 and extending for 4 months.
- Multiple events of malaria meeting the primary case definition over a period starting 14 days after Dose 3 and extending for 4 months.
- Multiple events of malaria meeting the secondary case definition over a period starting 14 days after Dose 3 and extending for 4 months.
- Parasite prevalence and density at 4½ months post Dose 3.
- Hemoglobin at 4½ months post Dose 3.

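### The only planned group comparison for hemoglobin is an unadjusted Wilcoxon test, which leaves screening hemoglobin and study center unused and names no between-group difference as the estimate

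*Protocol*

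**What the plan says.** Protocol Section 10.2 lists "Hemoglobin at 4½ months post Dose 3" among the secondary efficacy endpoints. Section 10.3 makes hemoglobin at 12 months and at the autumn 2008 survey tertiary.

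Section 10.9.3 covers all three surveys. For hemoglobin, "Hemoglobin mean and standard deviation will be presented" and, in the same sentence, "95% confidence intervals will be calculated"; the quantity that the intervals refer to is not stated. The group comparison follows: "The effect of the group will be evaluated using a non-parametric Wilcoxon test". Sections 10.10.1 and 10.11.1 send hemoglobin back to Section 10.9, so no other comparison is planned.

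In the next paragraph of Section 10.9.3, parasite density gets a named estimate: "Difference in geometric mean and 95% CI will be estimated". Sections 10.9.1 and 10.9.2 plan crude and covariate-adjusted estimates for the Cox and Poisson analyses (for the latter, if appropriate).

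A baseline value exists. Section 5.2.2 says that checking eligibility is a step "which will necessitate a physical examination and blood sampling for assessment of hematology, renal and liver function". The Table 3 note on the complete blood count, which is taken at Clinic Visit 1, reads "Includes analysis of hemoglobin, total white cell count and platelets". Table 6 plans screening safety bloods for 890 children, and Section 5.5 has the hematology values documented on the CRF. Section 6.4.1 gives each site a separate randomization list.

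Section 10.9.5 lists study center but not screening hemoglobin among the covariates, and leaves the choice of adjustment covariates to the Report Analysis Plan.

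**The concern.** A two-sample Wilcoxon test returns a p-value on the survey values alone. Two things are given up.

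The first is precision. Each child's screening hemoglobin is on file, and center already structures the randomization. If either is related to hemoglobin at the survey, leaving it out gives a wider interval and less power than the same children could provide. Center deserves particular attention at Clinic Visit 9, which is held in September in Korogwe and October in Kilifi.

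The second is a declared estimate. A reader of the results will want to know by how many g/dL the groups differ, and with what uncertainty. The protocol commits to such an estimate for parasite density, but for hemoglobin it commits only to group summaries and a test.

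What is at stake is how much the trial can say about one secondary endpoint and two tertiary surveys. Nothing here touches the malaria endpoints.

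**Working it through.** **1. The plan's own figure.** The protocol states no power for hemoglobin. Section 10.6.1 states 90% power for the primary endpoint: 400 evaluable per group, attack rates 36% and 25.2%, two-sided Fisher exact test at 5%. Exact enumeration gives 90.2%, and 400 × 0.36 + 400 × 0.252 = 244.8, the protocol's 245. The figure reproduces and does not depend on the hemoglobin analysis.

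**2. Inputs for hemoglobin.** n = 400 per group, borrowed from Section 10.6.1. The standard deviation is not given, so results are in SD units. The correlation r between screening and survey hemoglobin is not given either; r = 0.2, 0.3, 0.5 and 0.6 are assumptions. The contributions of center and age are not sized, because the protocol offers nothing to size them with.

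**3. Formulas.** Adjusting for the screening value multiplies the residual variance by 1 − r². The equivalent gain in sample size is 1/(1 − r²) − 1. The 95% CI half-width for the mean difference is 1.96 × √(2/400) × √(1 − r²), with 1.96 × √(2/400) = 0.139 SD unadjusted. The smallest difference detectable with 80% power at two-sided 5% is (1.960 + 0.842) × √(2/400) = 0.198 SD for an unadjusted mean difference; ANCOVA multiplies this by √(1 − r²). For the Wilcoxon test under normal data (efficiency 3/π = 0.955) it is 0.198/√0.955 = 0.203 SD.

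| Assumed r | Variance reduction vs. unadjusted mean difference | Equivalent extra children | CI half-width (SD) | Detectable difference, ANCOVA (SD) |
|---|---|---|---|---|
| 0.2 | 4% | 4% | 0.136 | 0.194 |
| 0.3 | 9% | 10% | 0.132 | 0.189 |
| 0.5 | 25% | 33% | 0.120 | 0.172 |
| 0.6 | 36% | 56% | 0.111 | 0.159 |

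**4. Direct comparison with the Wilcoxon test.** The variance column compares ANCOVA with an unadjusted mean difference, not with the test the protocol names. A simulation makes that comparison (4,000 runs per value of r, normal data, 400 per group, true difference 0.2 SD). Wilcoxon power was 78–79% throughout. ANCOVA power was 81% at r = 0, 84% at 0.3 and 91% at 0.5.

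**5. Where r is likely to lie.** Table 4 allows up to 60 days between screening and Dose 1. Clinic Visit 6 at Month 6½ therefore falls about 6½ to 8½ months after screening, and Clinic Visit 7 at Month 14 about 14 to 16 months after. Clinic Visit 9 (Months 14 to 19) can be later still. The children are 5 to 17 months old at first vaccination. Section 4.4 with Table 9 also excludes children with screening hemoglobin below 8.0 g/dL, which narrows the baseline range. Both features push r down, and it need not be the same at the three visits.

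**The case against.** The strongest reply is that nothing here is an error. The Wilcoxon test is valid under 1:1 randomization, makes no normality assumption, and is a defensible choice for a secondary endpoint. That stands. A reader might infer that the planned hemoglobin comparison is invalid or biased; the document does not support that. If hemoglobin were skewed, a rank test could even be the more efficient one, and the protocol gives no distribution.

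A reader might also infer that no effect estimate can be had. That goes too far. Section 10.9.3 promises 95% confidence intervals of an unnamed quantity, so an interval for the difference is not excluded, and a crude difference with its interval follows from the group means, standard deviations and numbers. What stands is that the protocol does not name that difference as the estimate, while it does so for parasite density.

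A third reply is that covariates are left to the Report Analysis Plan, which is not among the documents reviewed and could add an adjusted estimate. It could. But the comparison that the protocol itself fixes is a two-sample Wilcoxon test, which cannot carry a covariate, and screening hemoglobin is not on the Section 10.9.5 list.

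Two further inferences should be resisted. Nothing in the protocol shows that screening hemoglobin, center and age explain much of the spread in this age group. And the endpoint is hemoglobin level: no anemia endpoint is defined, so this is not a statement about an effect on anemia.

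**Conclusion.** The point holds as one of efficiency and reporting. The protocol fixes, as its only group comparison for hemoglobin, a valid test that sets aside a baseline value collected on every enrolled child and the site by which allocation was organized, and it names no between-group difference.

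The reporting part depends on no assumption. The precision part rests on a correlation that the protocol does not give: a 4% fall in residual variance at r = 0.2, rising to 36% at r = 0.6, relative to an unadjusted mean difference and with roughly normal data. Given the interval since screening and the entry limit, a gain near the lower end is plausible, and a large gain should not be promised. The primary analysis, the sample size and the stated 90% power stay as they are.

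**What to change.** Reword the hemoglobin paragraph of Section 10.9.3 in three respects:

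- Analyze hemoglobin by ANCOVA on group, with screening hemoglobin, study center and age as covariates.
- Report the adjusted mean difference (RTS,S/AS01E minus control) with its 95% CI at Clinic Visits 6, 7 and 9, and state that this difference is the estimate. If intervals for the group means are also wanted, say so separately.
- Keep the Wilcoxon test as a sensitivity analysis, which covers the case of skewed data.

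Add screening hemoglobin to the covariates in Section 10.9.5, and carry the same model into the Report Analysis Plan. The cost is wording and a small amount of programming. The covariates are already collected, and no visit, blood sample or sample-size change is involved.

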#### **10.9.4. Calculation of time at risk**

For efficacy endpoints, the time at risk will be counted in days, and expressed as person years at risk (days/365.25).

For each subject in the Total Cohort, time at risk begins 14 days after Dose 3 for those that received Dose 3 or 2½ months after Dose 1 (Day 75) otherwise. For the According to Protocol Cohort, time at risk begins 14 days after Dose 3.

The time at risk will end whenever one of the following conditions happen first: endpoint definition met, loss of follow up, emigration from the study area, withdrawal, death, end of follow-up period.

The time at risk will take into account absences from the study area and anti-malaria drug therapy. Absences from the study area of 1 week or more will be recorded in multiples of 1 week. The date of departure will be documented. Similarly, if treatment for malaria is administered, the subject will not be considered susceptible to malaria infection for the longest duration of the combination of drugs the subject could receive for this episode as follows: 28 days if received Coartem®, 28 days if having received sulfadoxine-pyrimethamine and 7 days if having received quinine alone.

If an episode is detected during a period of time not counting for the time at risk it will not be included in the analysis, however a table will be presented showing the number of such episodes not included in the analysis.

Episodes will be included in the analysis only if the subject is identified properly showing his/her ID Card at the contact with the health facility. Only blood slides that complete the reading process according to SOP will be considered in the establishment of endpoints.

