## **5.9. Active case detection (ACD) of Malaria**

Active Case Detection of malaria will commence two weeks post Dose 3.

At each visit the axillary temperature of each subject will be taken and if  $\geq 37.5^{\circ}\text{C}$  a blood slide and a rapid test (OptiMal®, Flow Incorporated, Oregon, USA) to determine malaria parasitemia will be taken.

If the child is documented to be febrile and the rapid test is positive, the field worker will give the child antimalarial chemotherapy and inform a study clinician. Mobile phones will be provided to study staff. Appropriate to the clinical features of the illness, transfer of children will be arranged to a health facility, if necessary. Amended 23 October 2006.

If the child is documented to be febrile and the rapid test is negative, antimalarial chemotherapy will not be administered by the field worker. A study physician will be informed. Appropriate to the clinical features of the illness, the child's parent(s)/guardian(s) will be advised to attend their nearest health facility to be reviewed by clinically qualified personnel (medical or nursing) or transfer will be arranged to the secondary care facility.

If the parents/guardians report the child has had a fever but the axillary temperature is  $< 37.5^{\circ}\text{C}$ , the field worker will revisit the child between 6 to 12 hours later to recheck the temperature and if the temperature is measured as  $\geq 37.5^{\circ}\text{C}$  a blood slide and rapid malaria test will be taken. If the test is positive, the child's case will be managed as above.

If no fever is documented at the revisit, a study physician will be informed. Appropriate to the clinical features of the illness, the child's parent(s)/guardian(s) may be advised to attend their nearest health facility to be reviewed by clinically qualified personnel (medical or nursing), or transfer will be arranged to the secondary care facility or on a study physician's advice, no further action is required. The parent(s)/guardian(s) will be informed that if they have concerns, they may always attend their nearest health facility to have their child reviewed by clinically qualified personnel.

Treatment will be indicated by rapid test result. Blood slides for parasitemia will not be read in real time to guide case management routinely. Blood slides will always be taken in duplicate.

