At any time at which a child is referred to a health facility, procedures for PCD will be followed (refer to Section 5.10).

All field worker visits and revisits will be documented in the CRF. Full details for ACD visits and operational methods will be given in site-specific SOPs.

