### **10.5. Case Definitions for Malaria**

**Primary malaria case definition** *P falciparum* infection > 2 500 parasites per  $\mu$ L in a child with a documented fever  $\geq 37.5^{\circ}\text{C}$  (axillary) detected by ACD or PCD.

**Secondary malaria case definition** *P falciparum* infection > 0 parasites per  $\mu$ L in a child with a documented fever  $\geq 37.5^{\circ}\text{C}$  (axillary) detected by ACD or PCD.

Amended 23 October 2006

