## **10.6. Estimated sample size**

### **10.6.1. Power Calculations**

The final analysis is projected to occur after the completion of 4 months of surveillance, at which time it is assumed that 36% of children in the control group will have been affected by a malaria episode. Assuming a true vaccine efficacy of 30% and an attack rate of 36% in controls (corresponding to an attack rate of 25.2% in vaccinees), a sample size of 400 evaluable subjects per group has 90% power to detect a difference between groups using a 2-sided Fisher exact test at 5% significance level. The final analysis is projected to occur after the completion of 4 months of surveillance, at which time it is assumed that 36% of children in the control group will have been affected by a malaria episode. However, in the event that malaria rates are lower in the year of the study, the unblinding and analysis will be delayed until approximately 245 children have experienced an episode ( $400 \times 36\% + 400 \times 25.2\% = 245$ ). This analysis will also have 90% power.

The assumption of 36% attack rate in controls is based on epidemiological data collected at the two sites. In Kilifi the proportion of children aged 12 to 18 months olds affected by a malaria episode using the same ACD methodology as proposed in this document over the same time frame in 2005 was 37% (personal communication [name]). In Korogwe the case rate was 34% determined in children aged 5 to 17 months in Mkokola village (10 km from Korogwe) by Passive Case Detection at village level (personal communication [name], [name]).

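### For the multiple-event malaria endpoints, the time-at-risk rule separates episodes only by antimalarial treatment, so one untreated illness can be counted twice

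*Protocol*

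**What the plan says.** The case definitions in section 10.5 require documented fever and a slide density above 2 500 parasites per µL (primary) or above 0 (secondary), "detected by ACD or PCD". They require no rapid-test result, no treatment and no interval since an earlier case.

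Section 5.9 bases field treatment on the rapid test; slides are not routinely read in time to guide care. "If the child is documented to be febrile and the rapid test is negative, antimalarial chemotherapy will not be administered by the field worker". Depending on the clinical features, the family is advised to attend a facility or the child is transferred, and "At any time at which a child is referred to a health facility, procedures for PCD will be followed". Under section 5.10, a child who is febrile at the facility has a rapid test and a slide. Table 3 schedules ACD visits weekly.

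Section 10.2 lists two repeat-event secondary endpoints, "Multiple events of malaria meeting the primary case definition over a period starting 14 days after Dose 3 and extending for 4 months" and "Multiple events of malaria meeting the secondary case definition over a period starting 14 days after Dose 3 and extending for 4 months". Section 10.3 repeats both definitions over 12 months and over the 2008 extension, which makes four tertiary endpoints. Section 10.9.2 tabulates children with 0, 1, 2, 3 and 4 or more episodes and fits a random-effects Poisson model.

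Section 10.9.4 ends time at risk when the endpoint definition is met, among other conditions. After an episode it removes time only on this condition: "if treatment for malaria is administered, the subject will not be considered susceptible to malaria infection". The window is 28 days for Coartem or sulfadoxine-pyrimethamine and 7 days for quinine alone. Absences of a week or more are also removed, but they do not separate episodes.

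**The concern.** A repeat-event analysis needs a rule that says when one illness ends and the next can begin. Section 10.9.4 offers two candidates, and neither works for these endpoints. The stop when the endpoint is met suits time to first case, but applied to repeat events it leaves nothing to count after the first. The treatment window works only if treatment is given, and section 5.9 describes a route on which a qualifying case goes untreated by the field worker and is sent on to be sampled again.

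The estimates at stake are the six multiple-event vaccine efficacies and the episode-frequency tables. They could count contacts where illnesses are meant. The definition with any parasitemia above 0 is the more exposed, because every positive slide qualifies. The definition above 2 500 per µL is less exposed, since both slides must exceed that density.

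**Working it through.** **The plan's own figure.** Section 10.6.1 states: "Assuming a true vaccine efficacy of 30% and an attack rate of 36% in controls (corresponding to an attack rate of 25.2% in vaccinees", and that a sample of "400 evaluable subjects per group has 90% power to detect a difference between groups using a 2-sided Fisher exact test at 5% significance level".

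- Exact power of the two-sided Fisher test by full enumeration (400 per group, 0.36 against 0.252): 90.2%, against 90% stated.
- Children with an episode: 400 × 0.36 + 400 × 0.252 = 144 + 100.8 = 244.8, against 245 stated.

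Both figures reproduce. Both count children with at least one episode, so a repeat count in the same child cannot change them. Time to first case is unaffected for the same reason.

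**Tracing one illness through the rules.**

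1. ACD visit: child febrile, rapid test negative, slide taken and later read above the threshold. Sections 5.9 and 10.5 make this a case. The field worker gives no antimalarial, so no window opens under 10.9.4.
2. Facility contact, or the next weekly ACD visit: child still at or above 37.5°C, and another slide is taken and later read above the threshold. Section 10.5 makes this a case too.
3. If treatment is given at step 2, its window starts there. It does not remove the event at step 1 or clearly merge the two.

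If time at risk continues after step 1, as section 10.9.2 needs for any second event, the result is two events with 0 excluded days between them.

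**Effect on counts and efficacy.** The documents give no rapid-test sensitivity, so the share f of illnesses counted twice is an assumption. Take a true rate ratio of 0.70, matching the 30% efficacy assumed in 10.6.1:

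VE = 1 − 0.70 × (1 + f_vaccine) / (1 + f_control)

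| f control | f vaccine | VE |
|---|---|---|
| 10% | 10% | 1 − 0.70 × 1.10/1.10 = 30.0% |
| 5% | 10% | 1 − 0.70 × 1.10/1.05 = 26.7% |
| 10% | 15% | 1 − 0.70 × 1.15/1.10 = 26.8% |
| 10% | 20% | 1 − 0.70 × 1.20/1.10 = 23.6% |
| 15% | 10% | 1 − 0.70 × 1.10/1.15 = 33.0% |

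The sign follows the arm with more duplication.

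**Effect on clustering.** If illnesses are Poisson and a share f is counted twice, the mean count is multiplied by (1 + f) and the variance by (1 − f) + 4f = 1 + 3f. The variance-to-mean ratio is then (1 + 3f)/(1 + f): 1.04, 1.10, 1.18 and 1.33 for f = 2%, 5%, 10% and 20%.

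**The case against.** The strongest reply is that 10.9.4 already prevents the double count. Time at risk ends when the endpoint definition is met, treated or not, and an episode found outside time at risk is excluded. Read literally, that is so. But the same reading excludes every second event, leaving the table and Poisson model in 10.9.2 with nothing beyond a first event. It cannot be the intended safeguard, and it shows that the section was not adapted to repeat events.

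A second reply is that merging repeat slides is a derivation detail for the Report and Analysis Plan, which is not shown. That plan may well add an interval. However, section 10.9.5 expressly defers the choice of covariates to it, whereas 10.9.4 defers nothing: it states the exclusion rule and ties it to treatment. The point is a stated rule with the wrong trigger.

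A third is that an episode is a larger unit than a contact, as the wording on drugs given for an episode suggests. That is a fair reading of intent, but no section gives an episode a duration or a minimum interval.

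Several limits stand:

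- A second count needs persisting fever and a second qualifying slide, and section 5.9 gives no timing for the facility visit.
- The facility repeats the rapid test and treats as required, which may close the route before any third count.
- Random effects, and the alternatives planned for lack of fit, absorb some of the clustering, though they do not correct counts that differ by arm.

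**Conclusion.** The point holds for the two secondary and four tertiary multiple-event endpoints. On one reading of 10.9.4 repeat events are barred; on the other, one untreated illness can be counted twice. The section needs correcting on either reading.

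The size is unknown. Equal duplication inflates counts and clustering and leaves efficacy at 30% in the illustration. Unequal duplication shifts it, for example to 26.8% at 10% control against 15% vaccine. These figures rest on an assumed rate ratio of 0.70 and assumed duplication shares.

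A reader might infer more, and the documents do not support it:

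- *That efficacy will be understated.* This needs more duplication in the vaccine arm. The documents give no rapid-test performance by arm, and the opposite imbalance would overstate efficacy.
- *That duplicates will be common, or will usually arise on the same day.* No frequency or timing is given, and not every test-negative illness need yield a duplicate.
- *That the main result is at risk.* The primary endpoint, the 90% power and the 245-child count all rest on first episodes.

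This is a correction worth making before analysis, not a threat to the trial's main conclusion.

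**What to change.** Amend 10.9.4 for the multiple-event endpoints only:

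- Replace the stop at meeting the endpoint definition with a not-at-risk window. It opens at any contact meeting that endpoint's own case definition, whether or not treatment was given.
- Apply it separately to the two case definitions, so that a low-density contact does not remove a later event above 2 500 per µL.
- Fix the length in advance, for example the 28 days already used for two of the drugs. If a later treatment window ends after it, extend to that date. Then resume time at risk.
- Treat qualifying contacts inside the window as the same episode, and report how many were merged beside the table of excluded episodes already planned.
- Add a sensitivity analysis with a shorter window, for example 7 days.

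The cost is a short paragraph and some programming, using data already collected. The downside is that true reinfections inside the window are merged. An untreated child has no drug effect to justify 28 days, so the length is a convention, and the shorter-window analysis shows how much it matters. The change is analytic and implies nothing about how children are managed.
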